### Procedure

The procedure is outlined in Fig. 1. Preliminary screening will be conducted over the telephone by one of the researchers. Volunteers who are deemed eligible will be scheduled a first visit. All participants will undergo the following physiological and functional assessments including lower-limb strength and proprioception, functional and balance tasks and executive function tests. Moreover, measures of physical activity, quality of life, pain and function, fear of falls, as well as falls history, will also be recorded. Participants’ satisfaction with the exercise program and their perception of improvement will also be assessed at the follow-up visit at the completion of the 8-week intervention. Figure 2 outlines the study design schedule in accordance with the SPIRIT Figure.

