**Fig. 2 Fig2:**
[figure not shown]
Study design schedule in accordance with the Standard Protocol Items: Recommendations for Interventional Trials (SPIRIT) Figure

Participants will first attend the Victoria University Footscray Park campus for baseline testing. During the first visit all measures, excluding strength, will be assessed. Familiarisation with the strength test will be conducted in the first visit followed by actual testing during a second visit (approximately 3–6 days apart). A set of questions to assess cognitive impairment (memory) will also be conducted in the initial visit using the SLUMS test where participants who score below 25 cut-off scores will be excluded from the study [11]. In the second visit, after completion of the strength test, participants will be randomized to one of the three groups: (1) high-speed resistance-training (HSRT) or (2) high-speed resistance-training and balance exercises (HSRTB) or (3) control group (no intervention). All eligible participants will complete the Exercise and Sport Science Australia (ESSA) exercise screening tool to evaluate any contraindicated medical conditions to exercise (https://www.essa.org.au/wp-content/uploads/2011/09/Screen-tool-version-v1.1.pdf). Participants answering “yes” to any of the screening questions will be required to obtain medical clearance from their local physician prior to participation in the intervention. Only participants randomized to one of the exercise intervention groups will need to obtain medical clearance if deemed relevant. Participants in the exercise intervention groups will attend Victoria University Exercise Rehabilitation Clinic twice a week for 8 weeks (total of 16 exercise sessions). Participants from the control group will be advised to continue with their usual activities. All participants will be reassessed after 8 weeks from the baseline assessment.

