### Pain-level documentation, exercise-stopping rules and adverse events

Pain level will be recorded using the NRS (0–10) during the sessions, 2 h and 24 h later. Any substantial increase in pain will be recorded. Pain-relief medication usage will be recorded via logbook by the participants during the intervention period.

The present study protocol will use similar principles to record pain and safety as reported in a previous dose-response trial in people with knee OA [19]. Substantial increases in pain will be defined as knee pain of at least 7/10 and or pain increased by at least 2–3/10 points (3/10 if initial pain is between 0 and 6/10 and 2/10 if initial pain is between 7 and 8/10) during the sessions, 2 h and 24 h after an exercise session as detailed below. The thresholds of 3/10 and 2/10 are based on a previous study suggesting that 2/10 represents a clinically significant change in pain and varies depending on the initial level [20].

An exercise-stopping rule will be defined as an incident (due to substantial increase in pain or an adverse event) that stopped the participant from completing the prescribed exercise for safety reasons and is likely to be related to the exercise program [19].

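### Follow-up is timed from baseline, not from the last training session, so exercisers can be tested within a day or two of a session, or before finishing the programme, while controls have no sessions

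*Protocol article*

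**What the plan says.** The Procedure section times the follow-up visit in two ways. The text after Fig. 2 counts from baseline: "All participants will be reassessed after 8 weeks from the baseline assessment". The opening paragraph, describing the satisfaction questions, places them "at the follow-up visit at the completion of the 8-week intervention". Design and setting gives a third form, 8 weeks after participation begins.

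Baseline itself is spread over two visits. On the first, "During the first visit all measures, excluding strength, will be assessed". Strength is rehearsed at that visit, with "actual testing during a second visit (approximately 3–6 days apart"). Randomisation follows the strength test at visit 2. Exercisers with a positive screening answer must then obtain medical clearance, and the section on the exercise protocol allows up to two familiarisation sessions before the intervention begins. Only after that does training run "twice a week for 8 weeks (total of 16 exercise sessions"). Controls continue their usual activities.

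The protocol anticipates pain after sessions: "Pain level will be recorded using the NRS (0–10) during the sessions, 2 h and 24 h later". It also has a rule for substantial pain lasting beyond 24 h. The last phase, weeks 6–8, carries the highest load band in Table 1. The text shown states no interval between the last session and the follow-up tests.

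**The concern.** An 8-week programme that starts some days after baseline does not finish 8 weeks after baseline. If the baseline rule is followed, the follow-up date can fall on a training day, the day after one, or before all 16 sessions are done. Only the two exercise arms are exposed to this, so randomisation does not balance it.

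The outcomes open to it are the follow-up pain scores and the tests that need maximal or fast effort: the 3RM leg press, 30 s chair stand, stair climb and stepping tests. Residual pain or fatigue would tend to make the programmes look more painful and less effective, and testing before the programme ends would understate its full effect. The Statistical analysis section compares pain, strength, balance and function between groups over time and uses the results for the power calculation of a later trial. A distortion here would carry forward into that design.

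**Working it through.** **Figures the plan states.** 2 sessions × 8 weeks = 16, and the phases give 4 + 6 + 6 = 16. 3 groups × 10 = 30. Both reproduce. The plan states no SD, effect size or power, so the size of any effect cannot be derived from it.

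**Timeline.** Let visit 1 be day 0 and let
- V = day of visit 2: 3 to 6 (Procedure);
- D = days from visit 2 to the first training session: 0, 3 or 7 (assumed; the article gives no time for clearance or familiarisation);
- S = days between the two sessions of a week: 1, 3 or 4 (assumed).

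The first session of week 8 comes 49 days after the first session of week 1, so

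last session = V + D + 49 + S.

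Gap to testing, counting 56 days from visit 1: 56 − (V + D + 49 + S) = 7 − V − D − S.

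Gap to testing, counting 56 days from visit 2: V + 56 − (V + D + 49 + S) = 7 − D − S.

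| V | D | S | Last session (day) | Gap, from visit 1 | Gap, from visit 2 |
|---|---|---|---|---|---|
| 3 | 0 | 1 | 53 | +3 | +6 |
| 3 | 0 | 3 | 55 | +1 | +4 |
| 3 | 3 | 3 | 58 | −2 | +1 |
| 6 | 0 | 3 | 58 | −2 | +4 |
| 6 | 3 | 3 | 61 | −5 | +1 |
| 6 | 3 | 4 | 62 | −6 | 0 |
| 6 | 7 | 4 | 66 | −10 | −4 |

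A negative gap means that the nominal date comes before the last session.

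- **From visit 1:** with sessions at least 2 days apart, the largest gap is 7 − 3 − 0 − 2 = 2 days, and that needs training to start on the day of randomisation. Over all 18 combinations (V = 3 or 6, with the D and S values above), 13 gaps are negative, 3 are zero and 2 are positive. This describes the grid and is not a probability.
- **From visit 2:** the range is +6 to −4. With D = 3 and S = 2 to 4, the gap is 7 − 3 − S = 2 to 0 days.

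**One case in full.** Take V = 3, D = 3, S = 3. Sessions fall on days 6 and 9 and then weekly from each, so those of week 8 are on days 55 and 58. Day 56 is the day after session 15, with one session still to come.

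**The other wording.** Testing at completion of the intervention ensures that the sessions are finished. It still permits a test on the day after the last one, so choosing between the two wordings does not settle the gap.

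**What a distortion could do to the next trial (assumed figures only).** For two-sided 5% and 80% power, n per arm = 2 × (1.960 + 0.842)² / d² ≈ 15.70 / d². With a true standardised difference of 0.5, n = 63. If an acute effect hid 0.1, 0.2 or 0.3 SD, the difference seen would be 0.4, 0.3 or 0.2, and n would be 99, 175 or 393. With no acute effect, n stays at 63.

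**The case against.** The strongest reply is that this is a condensed article, that the flow diagram and the schedule figure are not shown, and that exact test windows usually sit in the full protocol. Nothing says that anyone is tested on or just after a training day, and gaps of several days are possible. This stands against the stronger reading a reader might infer, that exercisers are tested unrested and that pain and fatigue do enter their scores. The documents support only that they can. It does not remove the point, because the article states a rule for the date, and that rule conflicts with its other statement and with its own sequence of visits.

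A reader might also take the 3–6 days at baseline as a rest period that follow-up lacks. The text does not support that. The interval separates strength rehearsal from the strength test, applies to strength only and to all participants before randomisation, and is not described as recovery. Every other measure is taken at visit 1.

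Nor is there support for a stated size. One could note that, during a training week with sessions at least 2 days apart, 4 of 7 days are a session day or the day after. Multiplying by a supposed rise of 1–2 NRS points gives 0.6–1.1 points. But the rise has no source in the document, test days need not be evenly spread, and the day count applies only while training is still running.

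Finally, the claim cannot cover every comparison. The document gives no reason why the cognitive tests, quality of life or the physical activity questionnaire should respond in this way.

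**Conclusion.** The point holds in limited form. The timing statements conflict, and the baseline rule leaves the interval between last session and testing uncontrolled: at most 2 days when counted from visit 1 with sessions at least 2 days apart, and +6 to −4 days when counted from visit 2 over the delays and spacings assumed. Only the exercise arms are exposed. The contrasts with control for pain and effort-dependent tests can be biased, probably against exercise, by an amount that the documents do not allow one to estimate and that may be zero.

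The primary measures (completion, attendance, dropout, exercises stopped, adverse events) do not depend on the follow-up test date as a source of acute pain or fatigue. The affected measures are secondary and exploratory at 10 per arm. The point still deserves action because those contrasts are meant to inform the next trial's power calculation and the remedy is cheap. It rests on the baseline rule being followed as written; a window in the full protocol tied to the last session would answer it.

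**What to change.** Reconcile the two statements in the Procedure section, and the matching one in Design and setting, so that there is one anchor.

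- **Exercise arms:** time the follow-up tests from the last scheduled training session, with a stated minimum gap and a window. At least 3 days would serve as an example; it is a convenient figure and not one that baseline used for recovery.
- **Controls:** test at a fixed time from randomisation that matches the planned exerciser schedule. For example, if the plan allows 3 days to start, 3 days between weekly sessions and a 3-day gap, that is 3 + 49 + 3 + 3 = 58 days after randomisation.
- **Record** the date of the last session and of testing for every exerciser, so that the actual gap can be reported.

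The training schedule does not change. The cost is a short scheduling rule and one extra recorded date. The visit may fall later: with a 3-day minimum the shift is 3 minus the gap above. That is 3 − 3 = 0 to 3 + 10 = 13 days beyond the date counted from visit 1, and none to 3 + 4 = 7 days beyond the date counted from visit 2. Start-up delays differ between people, so elapsed time from randomisation will still vary somewhat among exercisers; the recorded dates will show by how much.

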## Recruitment

Participants will be recruited from the general community and from the western suburbs of Melbourne. Advertisements in local newspapers will be used for recruitment. In addition some participants will be recruited from the staff body at Victoria University through advertisements in University publications and posters displayed on notice boards, as well as global emails to staff and students, and social media. Advertisements will also be placed in health care facilities and places with high circulation of senior citizens and will also be mailed-out to health care practitioners in Melbourne.

### Randomisation

All participants will be randomly allocated to one of the following groups: (1) HSRT or (2) HSRTB or (3) control group (no intervention). Block randomisation will be undertaken using opaque envelopes, so that blocks of six to seven participants (two to three for each intervention group and two to three for control group) will be randomized at a time. As participants will either be doing one of two different exercise programs or not doing an exercise program, assessors and participants will not be blinded to their respective group allocation.

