### Exercise interventions

#### High-speed resistance training (HSRT)

Participants who are randomized to the HRST will receive an exercise program that includes six to eight exercises targeting the lower limbs, to be performed twice a week for 8 weeks. The exercise sessions will be delivered by a qualified exercise physiologist or physiotherapist. The exercise program will include the following exercises: leg press, squat, step-up, lunges, going up stairs, sit to stand, calf raises (Table 1). Participants will be instructed to perform the exercises in a rapid and explosive manner such that all repetitions for each shortening phase (concentric activation of the muscle) will be performed as quickly as possible while the lengthening phase of the muscle (eccentric phase) will be controlled over 2–3 s. Several previous research trials have used similar principles of a high-speed training program for older people and those with knee OA and reported the training to be beneficial for older people, safe and with no adverse events [12–14]. However, none of the above studies investigated the effect of high-speed power training on balance or physiological risk factors for falls in this patient group, nor did they include functional weight-bearing exercises.

**Table 1 Tab1:** Details of the exercises and progression of the high-speed resistance program in the three phases

Exercise	% 1RM	Sets × repetitions	Progression
Phase 1 – week 1–2 (4 sessions)			
Bilateral leg press	20–40%	2 × 8–12	Load to be increased by 5–10% (of 1RM or % of BW) once participant reaches the upper limit of repetitions during their last set of each exercise with correct technique and velocity of contraction. All weight-bearing exercises will begin using bodyweight only ^a^height of chair/step adjusted to participant’s ability
^a^Step up		2 × 8–12	
^a^Sit to stand		2 × 8–12	
Calf raise		2 × 8–12	
Phase 2 – week 3–5 (6 sessions)			
Bilateral leg press	40–60%	2 × 5–8	Load to be increased by 5–10% (of 1RM or % of BW) once participant reaches the upper limit of repetitions during their last set of each exercise with correct technique and velocity of contraction. All weight-bearing exercises will begin using bodyweight only
^a^Step up		2 × 5–8	
^a^Sit to stand		2 × 5–8	
Calf raise			
^b^Squat		2 × 5–8	
^b^Stair climbing		2 × 5–8	
^b^Lunge		2 × 5–8	
Phase 3 – week 6–8 (6 sessions)			

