## Secondary outcomes

Demographic information including falls history (and associated information surrounding circumstances of falls), duration of joint symptoms, comorbidities, medical conditions and medications will be collected.

The following functional, physiological and cognitive tests will be assessed at baseline and at the follow-up assessment. These selected tests are key measures used to identify risk of falls:Leg strength and endurance will be assessed using the 30 s chair stand test. Participants will sit on a chair (a 43-cm high chair) and stand up, then repeat, as many times as they can for 30 s (no upper limb support), the number of sit to stand efforts performed will be recorded [21]Physical function will be assessed using the Timed Get Up and Go Test (with and without dual tasks (manual and cognitive)) [22]. Participants will stand up from a chair, walk 3 m as quickly and safely as possible, cross a line marked on the floor, turn around and walk back and sit down. This test will also be performed when carrying a glass of water (manual dual task) and when counting backward by 3’s (cognitive dual task). The time taken to complete the task will be measured with a stopwatch. One practice trial will be given followed by an actual testA rapid dynamic weight shift, coordination and stepping will be assessed using The Four Square Step Test (FSST) of balance [23]. Participants will step as fast as possible into four squares marked on the floor with tape (labeled 1–4) in a certain sequence (starting from square 1 then 2, 3, 4, 1, 4, 3, 2 and 1). This sequence requires the participant to step forward, backward, and sideways to the right and left. The score will be recorded as the time taken to complete the sequenceFunctional muscle power will be assessed using the Timed Stair Climb Test (10 steps, 14-cm rise). The time taken to complete the task (climb 10 steps as quickly as possible) will be recorded and the stair climbing power will be calculated using a formula described in previous research [24]Static balance will be assessed by evaluating postural sway of the body in the medio-lateral (M/L) and anterior posterior (A/P) directions using a swaymeter while standing on a medium-density foam rubber mat (70 × 60 × 15 cm thickness) with the eyes open and closed. The total excursion of the sway in each direction is measured in millimeters [25]Knee proprioception will be measured during sitting by matching the position of the legs on either side of a clear plastic sheet with the eyes closed [3]. Any error in matching the limbs will be recorded in degrees. After two practice trials, the average of five trials will be recordedThe ability of older people to step maximally and rapidly in multiple directions will be assessed using the Maximum Step Length and Rapid Step Test [26]. Initially, the maximum step length in the front, side and back directions will be assessed. With arms crossed over the chest, the participant will step maximally with one leg while keeping the other leg planted and then to return to the initial position in one step. The test will be repeated for each leg in three directions (front, side, back). Three practice trials will be given followed by a series of five trials for each leg in each direction. The step length will be measured and the average of the five trials will be used for the rapid step test. For the rapid step test, marks on the floor will be placed at 80% of the maximum step length measured previously in each direction. Participants will then step as fast as possible with one leg in a given direction on the marks on the floor as instructed by the assessor. A practice set of four steps for each leg will be given. The actual testing will include a series of 24 steps randomly selected by the assessor which will include four steps in each direction for each leg. The total time taken to complete the step sequence and any errors will be measured. An error will be defined as (1) loss of balance, (2) failure to return to the initial position, (3) multiple steps and (4) noncompliance with direction or sideLower-limb muscle strength will be assessed by having participants perform three maximal repetitions (3RM) during bilateral leg press using a seated leg-press machine. The maximum amount of weight lifted by participants through three full-range repetitions while maintaining correct technique will be used for determining the participant’s maximum 3RM strength. Participants will have a familiarisation session before the actual recording of the 3RM test. During the familiarisation session participants will be shown the correct exercise technique and be given the opportunity to familiarise themselves with the exercise. Initially, each participant will perform a warm-up set of eight repetitions on the leg press with a light load. This will then be followed by the completion of five to six repetitions at a heavier weight and rest period of 2–3 min. The load will be increased incrementally until only three repetitions with correct technique are able to be completed

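### Outcome assessors are left unblinded for a reason that applies only to participants, which exposes the week-8 performance tests to detection bias that could be reduced

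*Protocol article*

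**What the plan says.** The Randomisation section gives the reason and the decision in one sentence: "As participants will either be doing one of two different exercise programs or not doing an exercise program", and therefore "assessors and participants will not be blinded to their respective group allocation".

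Other parts of the protocol article bear on this:

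- **Timing (Procedure, text after Figure 2):** "In the second visit, after completion of the strength test, participants will be randomized to one of the three groups". All other baseline measures are taken at the first visit.
- **Delivery of training (High-speed resistance training):** "The exercise sessions will be delivered by a qualified exercise physiologist or physiotherapist". The article does not say who performs the outcome assessments, or whether these are the same people.
- **Outcome tests (Secondary outcomes):** for the Timed Get Up and Go, "The time taken to complete the task will be measured with a stopwatch". For the leg-press strength test, "The load will be increased incrementally until only three repetitions with correct technique are able to be completed". For the Rapid Step Test, "The actual testing will include a series of 24 steps randomly selected by the assessor", with errors also recorded.
- **Use of the results (Statistical analysis approach):** selected outcomes, including strength, balance and physical function, go into a repeated-measures ANOVA with group and time as factors. The results are to support power calculations for a later, fully powered trial. Feasibility and safety, the primary measures, are summarised descriptively.

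**The concern.** Participants in an exercise trial with a no-intervention control cannot be kept unaware of their arm. Assessors often can be, because they need to meet the participant only at the test visit. The article treats the two as one case and justifies both with the participants' situation.

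An assessor who knows the arm can, without intending to, encourage more warmly, start or stop a timer slightly differently, accept a borderline repetition, overlook a stepping error or choose an easier run of steps. If such effects differ by arm, they become part of the between-group difference. Estimating those differences for the next trial is a stated purpose of this pilot, so a bias would carry forward into that trial's sample size.

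**Working it through.** **1. Does the stated reason cover assessors?** The reason concerns what participants do. Nothing in it concerns the person who tests them. The article mentions no shared staffing between training and testing, no logistical obstacle and no safeguard such as a script or a separate tester.

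**2. When does the exposure arise?** Allocation follows the baseline strength test, and the other baseline measures come earlier still. Knowledge of the assigned arm can therefore act only on the week-8 measurement, and so only on one side of the pre-post change.

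**3. Which outcomes depend on the assessor?**

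| Test | Where the assessor enters | What the article standardises |
|---|---|---|
| Timed Get Up and Go | Hand timing, encouragement | Stopwatch named; one practice trial |
| Four Square Step, stair climb | Timing, encouragement | Fixed step sequence; fixed number of steps. Timed, device not named |
| 30 s chair stand | Count, encouragement | Chair height; no arm support |
| 3RM leg press | Technique judgement that ends the test | Three full-range repetitions |
| Rapid Step Test | Step sequence, error calls | Four listed error types; four steps per direction per leg (4 × 3 × 2 = 24) |

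Standardisation is partial. In each test some assessor discretion remains.

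**4. Where do these outcomes go?** They are of the kind entered in the group-by-time ANOVA, and from there into the future power calculation. The primary measures (completion, attendance, dropout, exercises stopped, adverse events) do not come from the week-8 tests.

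**5. How large could the effect be?** The only relevant figure in the article is the pilot's size, and 3 × 10 = 30 agrees with the stated total. The article gives no effect size, SD or bias, so what follows is a sensitivity range on assumed inputs and not an estimate. Let d be the true standardised difference and b the bias added by the assessor, both in SD units. Take two-sided alpha 0.05 and 80% power.

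- Planned n per arm = 2 × (1.960 + 0.842)² / (d + b)² = 15.70 / (d + b)², rounded up.
- Power at the true d = Φ(d × √(n/2) − 1.960).
- Example, d = 0.5 and b = 0: 15.70 / 0.25 = 62.8, so 63 per arm.
- Example, d = 0.5 and b = 0.2: 15.70 / 0.49 = 32.04, so 33 per arm. Power = Φ(0.5 × √16.5 − 1.960) = Φ(0.07) = 53%.

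Planned n per arm (power at the true d):

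| True d | b = 0 | b = 0.1 | b = 0.2 | b = 0.3 |
|---|---|---|---|---|
| 0.3 | 175 (80%) | 99 (56%) | 63 (39%) | 44 (29%) |
| 0.5 | 63 (80%) | 44 (65%) | 33 (53%) | 25 (42%) |
| 0.8 | 25 (81%) | 20 (72%) | 16 (62%) | 13 (53%) |

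**6. Compared with sampling error.** With 10 per arm, the standard error of a difference between two arms is √(2/10) = 0.447 SD. This is larger than any bias assumed above.

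**The case against.** The strongest reply is that this is an openly disclosed choice in a 30-person feasibility pilot. The primary outcomes are descriptive and largely untouched. Only exploratory secondary comparisons are exposed, and with a standard error of 0.447 SD they would be a weak basis for a sample size even with blinded assessors. Participants stay unblinded in any case, so their own effort, and their answers on pain, WOMAC, quality of life and fear of falling, would remain open to bias. The tests are partly standardised. Recruitment was under way when the article was written, so some week-8 visits may already be done.

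All of this stands, and it limits the point without removing it. Imprecision does not excuse a systematic error that can be reduced, and the article itself commits to using these differences for power calculations.

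A reader might also infer more than the article supports:

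- **That assessors are said to be impossible to blind.** The text says only that they will not be blinded.
- **That the future trial would be undersized by a known amount.** Every bias value in the table is assumed. The article fixes neither its size nor its direction.
- **That all timed tests use a stopwatch.** It is named only for the Get Up and Go.
- **That the assessor freely picks the steps.** The selection is described as random, and its composition is fixed. What is missing is a sequence generated independently of the assessor.
- **That full blinding needs no extra staff.** Staff numbers and assessor roles are not described.

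**Conclusion.** The point holds as a limited design weakness. The decision not to blind assessors rests on a reason that does not apply to them, and no safeguard accompanies it. The exposure is confined to the week-8 visit and to assessor-dependent secondary outcomes. It matters because those outcomes are compared between groups and used to plan the next trial.

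The size is unknown. On the assumed inputs, with a true difference of 0.5 SD, a bias of 0.1 to 0.3 SD would cut the planned size from 63 to between 44 and 25 per arm, and the real power from 80% to between 65% and 42%. This shows what a modest bias could do if the pilot estimate were used directly. It does not show that the bias exists.

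The change should be made because its core costs almost nothing. It is not a condition for the pilot to meet its feasibility and safety aims.

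**What to change.** For the remaining week-8 visits:

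1. Use scripted instructions and encouragement for every performance test, the same in all arms.
2. Replace the assessor-selected Rapid Step sequence with a pre-generated random order of 24 steps that keeps four steps per direction per leg.
3. Where existing staff allow, have the tests done by someone who neither delivered that participant's sessions nor opened the envelope. Ask participants not to disclose their arm, and record the assessor's guess of arm.
4. Where roles cannot be separated, state the assessor-specific reason in the Randomisation section in place of the present one. Name the limitation wherever the effect sizes are used for the future trial.

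Items 1 and 2 need one script and a printed step list, and no staff. Item 3 costs rostering effort and some scheduling flexibility, and depends on staffing that the article does not describe. A change during the trial also leaves a mix of earlier unblinded and later blinded visits, so the assessor's blinding status should be recorded per visit. Sample size, interventions and outcomes stay as they are.
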